## Abstract

**Introduction:**

Early decline of episodic memory is detectable in subjective cognitive decline (SCD). The left dorsolateral prefrontal cortex (DLPFC) is associated with encoding episodic memories. Repetitive transcranial magnetic stimulation (rTMS) is a novel and viable tool to improve cognitive function in Alzheimer’s disease (AD) and mild cognitive impairment, but the treatment effect in SCD has not been studied. We aim to investigate the efficacy of rTMS on episodic memory in individuals with SCD, and to explore the potential mechanisms of neural plasticity.

**Methods:**

In our randomized, sham-controlled trial, patients (*n* = 60) with SCD will receive 20 sessions (5 consecutive days per week for 4 weeks) of real rTMS (*n* = 30) or sham rTMS (*n* = 30) over the left DLPFC. The primary outcome is the Auditory Verbal Learning Test-Huashan version (AVLT-H). Other neuropsychological examinations and the long-term potentiation (LTP)-like cortical plasticity evaluation serve as the secondary outcomes. These outcomes will be assessed before and at the end of the intervention.

**Discussion:**

If the episodic memory of SCD improve after the intervention, the study will confirm that rTMS is a promising intervention for cognitive function improvement on the early stage of dementia. This study will also provide important clinical evidence for early intervention in AD and emphasizes the significance that impaired LTP-like cortical plasticity may be a potential biomarker of AD prognosis by demonstrating the predictive role of LTP on cognitive improvement in SCD.

**Ethics and dissemination:**

The study was approved by the Human Research Ethics Committee of the hospital (No. 2023-002-01). The results will be published in peer-review publications.

**Clinical trial registration:**

https://www.chictr.org.cn/, identifier ChiCTR2300075517.

## 1. Introduction

Alzheimer’s disease (AD), a neurodegenerative disorder of great concern in the context of the aging population, has come to be viewed not only as an isolated clinical diagnosis but as a multilevel process that changes along a sequential spectrum (Aisen et al., 2017). The earliest clinical manifestation in the spectrum of AD is subjective cognitive decline (SCD), also known as self-experienced memory disturbance without objective cognitive impairment (Wang et al., 2020). SCD is of great value when considered as an elevated risk factor for the development of AD dementia (Wolfsgruber et al., 2017; Wang et al., 2020), given that approximately 14.1% of individuals with SCD develop dementia in 4-year follow-up studies (Mitchell et al., 2014). These pathophysiologic changes occur many years before clinical signs of AD and it is likely that effective therapies at the stage of SCD will have the potential to slow or even halt the progression to AD (Si et al., 2020; Wang et al., 2020). Thus, SCD may be of utmost importance as a time node for early interventions in AD [6]. Based on the accumulating evidence from previous meta-analysis findings, non-pharmacological interventions have been widely used in individuals with SCD (Sheng et al., 2020).

Repetitive transcranial magnetic stimulation (rTMS), as a safe and reliable non-pharmacological intervention, has been shown to result in significant cognitive improvement in AD and mild cognitive impairment (MCI) in many research studies (Lin et al., 2019; Chou et al., 2020; Jiang et al., 2020). To date, rTMS over the left dorsolateral prefrontal cortex (l-DLPFC) has been shown to be an effective method of treatment in AD (Level C of evidence) (Di Lazzaro et al., 2021). The l-DLPFC is the most common choices for single site rTMS stimulation. A number of studies which targeted the l-DLPFC have shown significant improvements in cognitive function scores (Hauer et al., 2019; Lin et al., 2019; Zhang et al., 2022).

Episodic memory (EM) represents the ability to recall and recognize previously encountered objects, people, and events, and serves as a process that is critical for advanced cognitive functions such as judgment and decision-making (Wang, 2021; Lalla et al., 2022). In some studies, EM has been found to be a potentially sensitive indicator for pathological conditions such as AD (Tromp et al., 2015; Xue, 2018; Yu et al., 2021). It is also possible that EM may already be impaired relative to healthy controls (HC) in the SCD stage using the Auditory Verbal Learning Test-delayed recall (AVLT-DR), even when standardized memory tests show no decline (Zhu et al., 2021). Transcranial direct current stimulation (tDCS) and rTMS studies have shown that the dorsolateral prefrontal cortex (DLPFC) region plays an important role in strengthening EM associative memory and recall via reconsolidation in patients with dementia (Solé-Padullés et al., 2006; Vaqué-Alcázar et al., 2021). One previous research has demonstrated that the application of anodal tDCS on the left lateral prefrontal cortex (PFC) enhances pre-existing episode memories, with the effect persisting for a period of 30 days in elderly individuals with SCD (Manenti et al., 2017). Nonetheless, these results demonstrate the ability of the interventions to transiently influence brain function and did not identify them as therapeutic tools for individuals with memory impairment who performed poorly on neuropsychological tests (Solé-Padullés et al., 2006; Vaqué-Alcázar et al., 2021; Cotelli et al., 2022). Thus, to date, the efficacy of rTMS as a therapeutic tool for patients with SCD requires further investigation.

Previous studies have reported the varied neural mechanisms of rTMS for ameliorating cognitive impairment. rTMS may not only regulate the regulation of cortical excitability but may also lead to changes in cerebral blood flow, and neurotransmitters as well as the level of brain derived neurotrophic factor. Most importantly, rTMS may also alter synaptic plasticity and brain networks (Griskova et al., 2006). A Long-term potentiation (LTP) is one of the most extensively studied forms of synaptic plasticity (Wichmann and Kuner, 2022), and is the key cellular basis of the learning and memory process, which can be induced and evaluated simply by transcranial magnetic stimulation (TMS) protocols (Di Lorenzo et al., 2020b; Di Lazzaro et al., 2021). Large studies of patients with AD have demonstrated that changes in the LTP mechanism are linked to memory loss and increased levels of CSF tau. This association is particularly strong when coupled with the apolipoprotein E gene (APOE) ε4 polymorphism and progression of the disease (Francesco and Koch, 2021). Therefore, considering its potential as a biomarker for assessing synaptic impairment, TMS-assessed LTP may provide reliable information about related physio-pathological events in AD. Higher levels of CSF t-Tau of individuals with AD are linked with more powerful inhibition of motor evoked potentials, as induced by the 1 Hz TMS protocol (Koch et al., 2011). Moreover, LTP may be a as a predictive tool for revealing the progression of cognitive decline across the spectrum of AD (Motta et al., 2018). Previous studies have found that participants with MCI and amyloid positivity showed abnormal LTP-like plasticity with poorer memory function (Buss et al., 2020). These findings indicate the potential for utilizing LTP as a prognostic indicator or therapeutic target for the early stages of AD.

It is suggested that impairment to synaptic plasticity plays a crucial role in the development and progression of AD (Walsh and Selkoe, 2004; Shankar et al., 2008). According to Mecca et al. (2020) [^11^C]UCB-J PET technology demonstrated significant synaptic loss caused by AD at neocortical areas such as frontal regions. Another study suggest that cerebellar LTP-like cortical plasticity mechanisms are impaired in AD (Di Lorenzo et al., 2020a). Since the discovery of SCD, neuropathological abnormalities in amyloidosis (e.g., reductions in Aβ42 and increases in amyloid tracer uptake) and neurodegeneration have appeared. The latter includes atrophy in the medial temporal lobes and paralimbic and temporoparietal cortices (Rabin et al., 2017). The loss of long-term EM has not only been referred to as merely local damage to the medial temporal lobes, but also to the malfunction of cortical plasticity on the basis of memory processes (Vidal-Piñeiro et al., 2014). Considering the precocious impairment of plasticity mechanisms in AD, researching synaptic mechanisms in patients who show initial signs of memory deficits can effectively identify early functional anomalies, predict disease progression and evaluate the effectiveness of treatments. We, therefore, decided to study the change in LTP-like plasticity induced by SCD treatment with TMS.

The primary objective of our study is to investigate the efficacy of rTMS on EM in patients with SCD. The Auditory Verbal Learning Test-Huashan version (AVLT-H) will be used as the primary outcome measure. We also explore changes in the both neural and behavioral effects (other cognitive domains) after rTMS interventions. The predictive role of the LTP-like plasticity on cognitive improvement in rTMS-treated SCD patients will be studied. We hypothesized that stimulating the left-DLPFC (l-DLPFC) with 10 Hz rTMS can produce beneficial effects on EM in SCD by enhancing LTP-like plasticity.

## 2. Materials and methods

### 2.1. Study design

This is a randomized, double-blind, sham-controlled clinical trial, based on the Consolidated Standards of Reporting Trials (CONSORT) statement for non-pharmacologic therapy (Boutron et al., 2008). This study protocol was prepared in accordance with the Standard Protocol Items for Randomized Trials (SPIRIT) statement (Chan et al., 2015). The study was approved by the Human Research Ethics Committee at our hospital (No. 2023-002-01) and was registered with the Chinese Clinical Trial Registry (ChiCTR2300075517). Figure 1 shows details of the study design. Baseline (T0) assessments will assess demographic, behavioral, neurophysiological, and neuroimaging indicators and, following completion of the intervention program (T1), instantaneous outcomes will be measured and compared between the two groups. Patients will undergo a comprehensive clinical investigation including a medical history and a thorough neuropsychiatric assessment exploring cognitive domains (e.g., global cognitive function, language function, executive function, memory, and attention), neuroelectrophysiological examination via TMS before and after completion of the procedure. Cognitive tests and TMS test will be performed in the morning and afternoon on the same day, respectively.

**FIGURE 1 F1:**
[figure not shown]
Study flow diagram.

### 2.2. Participants

Enrollment of participants began in September 2023 from memory clinics, or surrounding communities. Right-handed participants will be screened and evaluated by a specialist using comprehensive neuropsychological test batteries at the Department of Rehabilitation Medicine of the Affiliated Jiangsu Shengze Hospital of Nanjing Medical University in China. All participants will sign a written informed consent before the program in accordance with the Declaration of Helsinki.

### 2.3. Eligibility criteria

The inclusion criteria are based on Jessen’s criteria as follows (Jessen et al., 2014; Shen et al., 2022): (1) not meeting the diagnosis of MCI on the standardized neuropsychological tests, including memory, speed/executive function, and language domains (Zhong et al., 2021); (2) self-perceived memory loss for at least 6 months; (3) presence of concern that performance in memory is worse than other people of the same age; (4) 55 to 80 years. The exclusion criteria are as follows: (1) clinical diagnosis of vascular dementia (Modified Hachinski Ischemic Score > 4) or dementia (NINDS-AIREN criteria); (2) drug or alcohol dependence within the last 6 months; (3) presence of severe cardiovascular or cerebrovascular disease or psychiatric disease; (4) contraindications to TMS; (5) treatment with antidepressants, anxiolytics, or central nervous system medications within 3 months prior to the assessments; (6) geriatric depression scale scores ≥ 6.

### 2.4. Sample size

According to Jia et al. (2021), the sample size was calculated using G*Power software, with a Cohen’s effect size of *d* = 0.7979 for rTMS on the 12-word Philadelphia Verbal Learning Test as the primary outcome (Jia et al., 2021). Moreover, alpha and power are set at 0.05 and 80%, respectively. Our study will increase the inclusion number by 10% to compensate for possible patient shedding. The final number of participants will be 30 per group.

### 2.5. Randomization and blinding

The randomization procedure will be performed by a researcher at a 1:1 balanced distribution ratio of (real or sham group) using a web-based randomization tool.^1^ Randomization information will be passed by sealed envelope until completion of the study. One investigator will oversee the random sequence and, at the intervention stage, the trained investigator will set the mode of the stimulus (real or sham group) according to the number on the paper in the envelope. Participants will be identified by codes rather than real names throughout the study. The neuroelectrophysiological assessor and the statistician will be blinded, as they are independently involved in the assessment or data analysis process, respectively.

### 2.6. Intervention

Repetitive transcranial magnetic stimulation (rTMS) treatment will be delivered using a D-MT500 magnetic biphasic stimulator (Neurosoft Ltd., Russia; peak magnetic field = 4T) equipped with an eight-shaped coil (AFEC-02-100-C; Neurosoft Ltd., Russia; diameter = 100 mm). Participants will randomly receive either rTMS or sham treatments over the l-DLPFC. The stimulation site is situated at the F3 point using the Bean F3 method as per the international 10–20 system for standardized placement of electroencephalogram (EEG) electrodes (Beam et al., 2009). Each treatment stimulation session consists of 10 Hz rTMS with 5 s train duration (50 pulses per train), and intertrain intervals of 10 s. In total, there are 40 trains with 2,000 pulses per day, 10 min each time, for 5 consecutive days per week for 4 weeks. Intensity will be set at 90% of the resting motion threshold (RMT) for each participant, defined as the minimum single-pulse intensity that triggers motor evoked potential (MEP) (not less than 50 μV) in at least 5 of 10 hotspots in the contralateral abductor pollicis brevis (APB) trial. The sham procedure is provided by the same device through a self-contained sham stimulus procedure. And the sessions are matched in all subjects.

The electromyography (EMG) system (Neuro-MEP-Micro, Russia) will be used to record the MEPs of the right-hand APB through surface Ag-AgCl electrodes. Through visual and EMG monitoring, entire relaxation of the muscle will be ensured. The coil is first placed on the left M1, and the handle placed backward at 45° against the midline of the sagittal plane of the brain. To determine the hotspot, where the lowest intensity induces the highest MEP amplitude, the coil is moved every 0.5 cm each time around the presumed scope. If the hotspot cannot be confirmed within 10 stimuli, the coil is shifted to the next location. Once the motor hotspot has been identified, the RMT will be determined.

### 2.7. Outcome measurements

#### 2.7.1. Primary outcomes

The Auditory Verbal Learning Test-Huashan version (AVLT-H) assessment will be used as the primary outcome to assess EM for our study. The AVLT-H assesses several aspects of verbal EM through a list of 12 words, such as short or long-term delayed recall and recognition. It has been widely used as a semantic categorization memory test in mainland Chinese populations (Li et al., 2016). The AVLT-H scores include AVLT-H immediate recall total score (AVLT-H-IR-S), AVLT-H short-term delayed recall score (AVLT-H-SR-S) with a 5-min delay time, AVLT-H long-term delayed recall score (AVLT-H-LR-S) with a 20-min delay time, AVLT-H total, and AVLT-H recognition score (AVLT-H-REC-S) (Zhao et al., 2012). This test has been proved to be a sensitive diagnostic evaluation of cognitive impairment (Li et al., 2016).

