### 2.8. Data analysis

SPSS V.23.0 will be used to analyze the data, and levels of statistical significance will be set at *p* < 0.05. For descriptive statistics, the Shapiro–Wilk test will be applied to check for normal probability prior to data entry. Data from the normal distribution will be reported as mean and standard deviation, whereas medians with interquartile ranges will be used to express the non-normal distribution. Categorical variables will be described as frequency as a function of percent. Demographic characteristics and baseline variables will be compared between the two groups using independent samples *t*-test or non-parametric Mann–Whitney test for continuous data, and comparisons of categorical variables using chi square or Fisher’s exact tests. Based on the existing literature, we can determine whether the unbalanced baseline data affect the results and, if so, conduct covariance analysis using the baseline data as covariates to control for the effect of potential confounders. The experiment will be analyzed using intention-to-treat (ITT) and missing data will be interpolated using multiple imputation method.

For normally distributed data, a repeated-measures analysis of variance (ANOVA) will be conducted to evaluate changes in treatment effect between and within groups (group: real vs. sham rTMS) (time: pre-vs. post-treatment). Alternatively, for non-normally distributed variables, we will perform the Wilcoxon signed rank test for within group comparisons, and the Mann–Whitney test will be applied to compare the effect between groups at each time point. In addition, we also aim to use a repeated-measures ANOVA to examine LTP-like plasticity as a function of percent change at four time points (last baseline, 5, 10, and 30 min after iTBS) between the two groups. *Post hoc* comparisons between groups will be used using the Bonferroni correction method. The generalized linear model (GLM) will be considered if the data is not normally distributed. To investigate the relationship between brain measurements and clinical cognitive function characteristics, we will perform correlation analyses by repeated measures linear regressions.

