The cortical plasticity is thought to be an important mechanism for information processing in brain neural networks during motor and skill learning (Haley and Maffei, 2018; Mansvelder et al., 2019). LTP could also account for the neurophysiological basis of highly connected node formation. Based on the outcomes of our unpublished research, we have found that LTP-like cortical plasticity was significantly reduced in an SCD group when compared with an HC group. High-frequency rTMS can excite neurons directly, and correspondingly lower the threshold for synaptic transmission, making the synapse quite active and increasing synaptic connections. Potentially, high-frequency pulses of rTMS could generally induce LTP and restore cortical plasticity (Suppa et al., 2015). Li et al. (2021) reported that the cognitive improvement in patients with AD which correlated with changes in LTP was significant after 6 weeks of treatment with 20 Hz rTMS. However, few studies have yielded the effects of rTMS on LTP-like plasticity in SCD. Therefore, the present study will measure motor cortex plasticity as a proxy for the general form of cortical plasticity to examine the effect.

In this protocol, we assess other domains of cognitive function except for the EM. The small degree of progress in these domains also shows important clinical implications. The results of this trial may provide a significant improvement in cognitive deficits among SCD. Because the effective intervention at the SCD stage could increase the potential for disease reversal, it is particularly important to explore a feasible method thereof. If the results are positive, as expected, this study will shed light on a new direction in cognition management in SCD.

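### The primary outcome is a five-score memory test with no score chosen and no multiplicity rule; if any one score may count, the false-positive rate is roughly 9-20% instead of 5%

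*Protocol article*

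**What the plan says.** Section 2.7.1, whose heading is in the plural, says of the AVLT-H that this "assessment will be used as the primary outcome to assess EM for our study". It then itemises the scores: "The AVLT-H scores include AVLT-H immediate recall total score (AVLT-H-IR-S), AVLT-H short-term delayed recall score (AVLT-H-SR-S"), the 20-min delayed recall, and "AVLT-H total, and AVLT-H recognition score (AVLT-H-REC-S"). That makes five. The Abstract and the last paragraph of the Introduction also name only the test.

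Section 2.8 says that "levels of statistical significance will be set at *p* < 0.05", without limiting this to one score. Its only multiplicity provision is a Bonferroni correction for post hoc between-group comparisons, placed directly after the analysis of plasticity over time points. It does not mention the AVLT-H scores.

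Section 2.4 says that "alpha and power are set at 0.05 and 80%, respectively". It uses one effect size, d = 0.7979, taken from the 12-word Philadelphia Verbal Learning Test, adds 10% for dropout and arrives at 30 per group.

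**The concern.** The sample-size section describes a trial with one primary comparison, and the outcome section does not define one. With five scores under the primary heading and no rule for combining or ranking them, the deciding score could be picked after the results are known.

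The Abstract's Discussion ties confirmation of benefit to improvement in episodic memory in general, without attaching it to a score. A significant difference on recognition alone, or on immediate recall alone, could therefore be reported as a positive primary result. The nominal 5% would then not describe the risk of a false claim, and a reader of the results could not tell whether the reported score had been chosen in advance.

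**Working it through.** **1. The plan's own figure.** Inputs from section 2.4: d = 0.7979, alpha 0.05 (taken as two-sided; the section does not say), power 80%, dropout 10%.

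- Normal approximation: n = 2(1.960 + 0.842)² / 0.7979² = 15.70 / 0.6366 = 24.7, so 25 per group.
- Two-sample t-test (noncentral t): 25.65, so 26 per group. With dropout, 26/0.9 = 28.9 or 26 × 1.1 = 28.6, so 29.
- Mann-Whitney test: 25.65/0.955 = 26.9, so 27 per group. With dropout, 27/0.9 = 30.

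The stated 30 per group is reproduced. It is the size for **one** comparison at 0.05. With 30 × 0.9 = 27 evaluable per group, t-test power at d = 0.7979 is 82%.

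**2. Upper bound for five tests.** If the five scores were independent, the chance of at least one false positive would be 1 − 0.95⁵ = 1 − 0.774 = 22.6%. This cannot be reached, because all five come from one test that "assesses several aspects of verbal EM through a list of 12 words".

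**3. Allowing for overlap.** The documents give neither the correlations nor the definition of the total. Assumptions: the four component scores share a common correlation r, and the total is the sum of the three recall scores. With equal standard deviations, the total then correlates with each recall score at √((1 + 2r)/3). That is 0.58 even at r = 0, and 0.82 at r = 0.5. Simulated chance of at least one of five two-sided tests at 0.05 being significant when there is no true effect (large-sample z tests):

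| r among components | At least one false positive |
|---|---|
| 0 | 20.2% |
| 0.3 | 18.1% |
| 0.5 | 15.9% |
| 0.7 | 13.1% |
| 0.8 | 11.5% |
| 0.9 | 9.4% |

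T-tests with 27 per group give nearly the same: about 21% at r = 0, 18% at 0.3, 16% at 0.5, 12% at 0.8 and just under 10% at 0.9. Summing all four components, or doubling the standard deviation of immediate recall, moves the z-test figures by about 0.2 percentage points at most.

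**4. If all five scores were kept as primary.** Bonferroni would test each at 0.05/5 = 0.01. Power at d = 0.7979 with 27 per group would be 60% for one given score. For at least one significant score, if the effect is present on all, it would be about 95% at r = 0.3, 89% at 0.5, 78% at 0.8 and 73% at 0.9. To keep 80% for one given score, 39 evaluable per group would be needed, or 39/0.9 = 43.3, so 44 enrolled.

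**The case against.** The best defence is that section 2.7.1 speaks of a single primary outcome, never says that any one score suffices, and may only be describing what the instrument yields. A separate analysis plan could name the score. This stands in part: the inflation is conditional, and no rate can be called the trial's actual error rate. It does not remove the point. The sample size depends on which variable is primary, and the article does give the outcome, its scores, the alpha and the place where correction applies. These statements do not fit one another.

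Four stronger readings are tempting but unsupported.

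- **That the error rate is as high as 23%.** This needs independent scores, which overlapping scores from one word list cannot be.
- **That the 80% power belongs to one unnamed AVLT-H score.** The effect size comes from another instrument and is tied to none of the five scores. The arithmetic behind 30 per group is sound.
- **That correcting for five scores cuts power to 60%.** This is the power for one given score at 0.01. Under the any-one-score rule that produces the 9-20%, the matching power is about 73-95%, if the effect is present on all scores.
- **That the other cognitive tests add a further error of the same kind.** The Discussion does say "The small degree of progress in these domains also shows important clinical implications", but the Introduction presents those domains as exploratory. Uncorrected secondary outcomes are ordinary, and no confirmatory claim is attached to them.

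**Conclusion.** The concern holds in conditional form. The primary outcome is a test with five overlapping scores, none chosen and none covered by a multiplicity rule, in a trial sized for one effect at 0.05.

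If significance on any one score is accepted as success, the false-positive rate is about two to four times the nominal level: roughly 9-20% overall, and about 12-16% for component correlations of 0.8 to 0.5. These figures rest on three assumptions that the document does not settle: the any-one-score rule, the correlations, and the total as a sum of the recall scores. No plausible choice of correlation brings the rate back to 5%. A positive primary claim would be hard to interpret if this is left open, so it should be settled before unblinding.

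**What to change.** Before unblinding, amend section 2.7.1 (and the registry entry, if it reads the same) to name one AVLT-H score, as change from T0 to T1, as the sole primary outcome, tested at two-sided 0.05. Make the other four scores secondary, with Holm's procedure or a fixed order if they are to carry claims.

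A delayed-recall score would fit the Introduction, which says that delayed recall may already show impairment at this stage. The Introduction gives no delay interval, and section 2.7.1 lists both a 5-min and a 20-min delay, so that choice is the trial team's.

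In section 2.4, state that the test is two-sided and that the 80% power assumes that d = 0.7979, taken from the Philadelphia Verbal Learning Test, holds for the chosen score. If it does, power is about 82% with 27 evaluable per group by two-sample t-test. Naming a score does not itself show that it does.

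If the team prefers to keep several scores as primary, it should state the multiplicity rule and the success criterion and re-power accordingly.

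Cost: wording only, with no added participants or assessments. The downside is that the four demoted scores can no longer carry the primary claim.
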